#### Child Rearing Practices Report–Questionnaire (CRPR-Q)

The *Child Rearing Practices Report–Questionnaire* (CRPR-Q; [30] is a 40-item parent-report questionnaire used to assess parenting practices that are theoretically and empirically linked to child developmental outcomes. Parents are instructed to respond with reference to a specific child in the household, rating each item on a 6-point Likert scale ranging from 1 (*strongly disagree*) to 6 (*strongly agree*). The measure comprises two theoretically grounded subscales: Nurturance, which captures parenting behaviors characterized by warmth, emotional availability, and expressions of affection (e.g., “I express affection by hugging, kissing, and holding my child”); Restrictiveness, which reflects parental emphasis on behavioral control, obedience, and caution in risk-taking (e.g., “I prefer that my child not try things if there is a chance he will fail”). Mean scores are calculated for each subscale, with higher values indicating greater levels of the respective parenting behavior. These dimensions are considered critical for understanding variability in children’s socioemotional, behavioral, and cognitive development. In the Portuguese adaptation of the CRPR-Q, the instrument demonstrated satisfactory internal consistency, with Cronbach’s alpha coefficients of .83 for Nurturance and .86 for Restrictiveness [28], supporting its reliability for use in developmental research within Portuguese-speaking populations.

#### Depression, Anxiety, and Stress Scale – 21 (DASS-21)

The *Depression, Anxiety, and Stress Scale – 21* (DASS-21; [19] is a 21-item self-report questionnaire designed to assess symptoms of depression, anxiety, and stress in parents. Each item is rated on a 4-point Likert scale ranging from 0 (*Did not apply to me at all*) to 3 (*Applied to me most of the time*). The scale comprises three subscales: Depression (7 items), which assesses dysphoria, hopelessness, devaluation of life, self-deprecation, lack of interest or involvement, anhedonia, and inertia; Anxiety (7 items), which measures autonomic arousal, skeletal muscle effects, situational anxiety, and the subjective experience of anxious affect; Stress (7 items), which evaluates chronic, nonspecific arousal, including difficulty relaxing, nervous arousal, irritability, agitation, and impatience. Subscale and total scores are calculated by summing the item responses. Both the original and Portuguese versions of the DASS-21 have demonstrated strong internal consistency, Cronbach’s alpha coefficients were 0.90 for the depression subscale, 0.86 for anxiety, 0.88 for stress, and 0.95 for the total score combining the three subscales, and construct validity [4].

#### Resource use

Resources used by children and their parents will be measured using a questionnaire adapted from published questionnaires [26]. Resource use will include healthcare services (accident and emergency visits, primary care and specialized outpatient visits and inpatient stays, medication), social services, transportation, absenteeism and presenteeism from both paid and unpaid work, and out-of-pocket expenses. This measure will be used for economic evaluation.

#### AQOL-8D: Assessing Quality of Life - 8 Dimensions [29]

Quality of life among caregivers will be measured with the Assessing Quality of Life - 8 Dimensions (AQOL-8D; [29] is a multi-attribute utility instrument developed to provide a sensitive and comprehensive assessment of health status among adults across eight dimensions,, including independent living, mental health, coping, relationships, pain, self-worth, happiness and senses) and 35 items with four to six response levels, each representing increasing levels of severity. This measure will be used for economic evaluation.

#### Evaluation of the intervention

Participants allocated to the VIPP-SD intervention will be invited to complete a feedback questionnaire upon the completion of the program. The evaluation of participant satisfaction will focus on their overall experience with the intervention, including their perceptions of the effectiveness of VIPP-SD and the suitability of the treatment setting.

#### Sociodemographic questionnaire

A Sociodemographic Questionnaire will be administered to collect background information on both the child and their parents. This will include data such as sex, age, nationality, household composition, socioeconomic status, and educational level.

### Data analysis

Data inspection procedures will be performed once the data collection is completed, but prior to the commencement of formal statistical analyses. These preliminary analyses will focus on examining the quality and integrity of the data collected, identifying any potential errors, outliers, or inconsistencies. Data validation steps will include checking for missing values, verifying the distribution of key variables, and ensuring adherence to predefined inclusion criteria. The results of this inspection will guide decisions on data cleaning, imputation, or any necessary adjustments before proceeding with more advanced statistical methods.

For all study objectives, the impact of the VIPP-SD intervention will be compared to the control condition using intent-to-treat (ITT) analyses. To assess the intervention's effect in the key outcomes, including parental sensitivity and sensitive discipline, child behavior problems (SDQ), depression, anxiety, and stress (DASS-21) and child rearing practices (CRPR-Q), we propose the use of a repeated measure ANOVA. In this model, experimental condition will be treated as a between-subjects factor, and assessment time-point as a within-subjects factor. The regression coefficient for the interaction between condition and assessment time will estimate differential changes in parental sensitivity and sensitive discipline between the intervention and control groups over time.

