## Methods

### Recruitment

One hundred and twenty families will be recruited from families attending Family Support and Parental Counseling Centers (CAFAP) and Child Psychology Centers in the Metropolitan area of Lisbon. CAFAP is a specialized social response aimed at supporting families with children and adolescents who are in situations of vulnerability, risk, or danger. CAFAP operates through referrals from entities such as Child and Youth Protection Commissions (CPCJ), schools, health services, or social security, with all interventions conducted in agreement with the legal guardians.

A minimum of 60 families in each condition will participate in the study, with an equal balance (through stratified randomization) of boys and girls. Inclusion criteria for parents will be: (1) fluency in Portuguese, (2) having a child between the ages of 2 and 6 years, and (3) absence of any diagnosed psychopathology, chronic or hereditary illnesses. Parents of children with a known diagnosis of disabilities, chronic or hereditary illnesses will be excluded from the study, since they are eligible for other intervention programs that are targeted to their specific needs. The expected completion date for participant recruitment is July 31, 2026.

We conducted a Power Analysis to ensure sufficient statistical power, based on previous VIPP studies. Expected effect size for primary outcome is meta-analytically *f* = 0.18 [38]. Assuming *f* = .18, power = .90, and *α* = .05, and correlation between pretest and posttest of *r* = .35, at least 54 participants per group are required. To account for attrition, we set a target of 60 per group.

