### Study design

To evaluate the intervention’s effectiveness, we will conduct a two-arm randomized controlled trial (RCT) in which participating families will be randomly assigned to either an intervention group or a control group ("dummy" contacts with interveners) after the baseline visit. Parents in the Control Group will receive, at the same frequency as the Intervention Group’s sessions, a phone call addressing topics related to child development (e.g., sleep, nutrition, etc., but not providing feedback on parenting). The protocols will be specifically designed to encourage participants to talk about their children. Randomization will be performed using a computer-generated random allocation sequence, stratified by child age and sex to ensure balanced group characteristics and group assignment will be done after the baseline assessment is completed to minimize potential bias (Fig. 1).

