### Instruments

Data collection for sociodemographic variables will take place at baseline (pretest). Parental sensitivity and sensitive discipline will be coded from videotaped mother–child interactions by independent, trained observers who are blinded to intervention conditions; these measures will be collected at baseline and immediately post-intervention (posttest). All other measures will be collected at three time points: baseline, posttest, and follow-up. Due to time and personnel limitations, the follow-up evaluation will rely solely on questionnaires.

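### Randomisation is stratified by child age and sex, but the repeated measures ANOVA names only condition and time; if age or sex predicts change, its tests are slightly conservative

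*Protocol article*

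**What the plan says.** All references are to the protocol article.

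- **Study design:** allocation is computer-generated and "stratified by child age and sex to ensure balanced group characteristics".
- **Recruitment:** at least 60 families per condition, "with an equal balance (through stratified randomization) of boys and girls".
- **Data analysis:** for the observed parenting measures, SDQ, DASS-21 and CRPR-Q, "we propose the use of a repeated measure ANOVA". Its factors are then given: "experimental condition will be treated as a between-subjects factor, and assessment time-point as a within-subjects factor". The effect of interest follows: "The regression coefficient for the interaction between condition and assessment time will estimate differential changes in parental sensitivity and sensitive discipline". Age and sex are not named as factors or covariates, and nothing excludes them.
- **Instruments:** sensitivity and discipline are observed at two time points, baseline and posttest. The other measures have three.
- **Recruitment (sample size):** f = 0.18, power 0.90, alpha 0.05 and a pretest-posttest correlation of 0.35 give at least 54 per group, raised to 60 for attrition.

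**The concern.** Stratified allocation makes the arms nearly equal on child age and sex, so any outcome variance due to these factors largely drops out of the difference between arms. A model without the strata still counts that variance as residual error. Its standard error then describes a less balanced design than the one actually run: intervals come out too wide and the test rejects too rarely. Both variables are known for every family at randomisation, so this is avoidable. With children aged 2 to 6 and discipline rated in a task meant to provoke difficult behaviour, it is plausible, though not shown in the article, that age or sex is related to how outcomes change.

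**Working it through.** **1. The plan's own figure.** For two groups and m = 2 time points, the noncentrality of the interaction test is lambda = f² × N × m / (1 − r), with 1 and N − 2 degrees of freedom. At N = 108, lambda = 0.0324 × 108 × 2 / 0.65 = 10.77 and power is 0.902. At N = 106 it is 0.896. So 108 in total, or 54 per group, reproduces exactly. At N = 120 power is 0.929. As a cross-check, f = 0.18 is a difference in change of 4 × 0.18 = 0.72 SD, and the SD of change is √(2 × 0.65) = √1.3. The normal approximation gives 53 per group. The sample size therefore matches the model with condition and time alone.

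**2. What cancels.** With two time points, the interaction test is a comparison of change scores (posttest minus baseline). An age or sex effect that is equal at both times subtracts out. The same holds for the interaction in the three-time-point outcomes. What remains is R², the share of change-score variance that age and sex explain. The article does not give it. I assume 0 to 0.10 and show 0.15 as an outer case.

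**3. Size of the effect.** Let V be the variance that the model without strata reports. Under stratified balance the true variance of the estimate is (1 − R²)V. With z = 1.96 and a standardised effect of 1.96 + 1.2816 = 3.2416 (power 0.90 on the normal approximation):

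- test size = 2 × P(Z > 1.96 / √(1 − R²))
- interval width relative to what is needed = 1 / √(1 − R²)
- power without strata = Φ(1.2816 / √(1 − R²))
- power with strata = Φ(3.2416 / √(1 − R²) − 1.96)
- sample-size factor k at which the model without strata matches the adjusted one: √k = 1 + 1.96 × (1 − √(1 − R²)) / 3.2416; gain per arm = 54 × (k − 1)

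| R² | Test size | Relative width | Power without strata | Power with strata | Gain per arm |
|---|---|---|---|---|---|
| 0 | 0.050 | 1.000 | 0.900 | 0.900 | 0 |
| 0.05 | 0.044 | 1.026 | 0.906 | 0.914 | 1.7 |
| 0.10 | 0.039 | 1.054 | 0.912 | 0.927 | 3.4 |
| 0.15 | 0.034 | 1.085 | 0.918 | 0.940 | 5.2 |

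**4. Simulation check.** N = 120, four strata (sex by two age bands, the banding being an assumption), balanced allocation within strata, r = 0.35, a change-score analysis with and without strata, 8,000 runs under no effect and 4,000 at 0.72 SD.

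- *Constant effects of 0.8 SD for each of age and sex, none on change:* interval width 0.823 without strata and 0.824 with; coverage 0.947 and 0.946; power 0.930 for both. Nothing is gained.
- *R² of change about 0.03:* width 0.836 against 0.822; power 0.917 against 0.924.
- *R² of change about 0.12:* width 0.879 against 0.822; coverage without strata 0.963; type I error 0.037 against 0.049; power 0.902 against 0.922. The actual SD of the estimate was 0.208 in both models.

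The formula in step 3 also gives a test size of 0.037 at R² = 0.12, in agreement with the simulation.

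**The case against.** The strongest objection is that a journal article condenses the plan and that covariate lists commonly sit in the analysis plan, which is not shown. Data analysis does not say that the model is unadjusted, so stratifying and this description do not contradict each other. That much stands. It does not dispose of the point, because the section positively names the model and its factors for all key outcomes, and the sample size reproduces from that same model.

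The second objection is that the chosen contrast already deals with most of what age and sex could contribute. This stands in full and limits the point to effects on change. The article offers no evidence that such effects exist.

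Three stronger readings are tempting, and the article supports none of them:

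- *Leaving out the strata necessarily costs precision, or wastes what stratification bought.* It does not. The estimate is equally precise either way (SD 0.208 in both models). Only the reported standard error is conservative, and only if R² for change is above zero.
- *Adjustment is worth 3 to 10 families per arm.* The formula 54 / (1 − R²) − 54 gives 2.8, 6.0 and 9.5 at R² = 0.05, 0.10 and 0.15. But it treats the unadjusted estimate as if it kept its full variance, when stratification has already reduced it. The consistent calculation gives 1.7, 3.4 and 5.2.
- *The cost and QALY regressions omit the strata.* The Health economic evaluation section lists no covariates at all, so no omission can be shown. Data analysis likewise does not mention confidence intervals for these outcomes; the widths above are simply what the standard errors imply.

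**Conclusion.** The point holds in a limited form and is minor. The described model leaves out the two factors on which allocation is balanced. Its standard errors are too large to the extent that age or sex predicts change, and by nothing if they do not. Over the assumed range of R² from 0 to 0.10, intervals are 0 to about 5% wider than needed, the test size lies between 5% and about 3.9%, and the gain from adjustment is 0 to about 3 families per arm (about 5 at 0.15). The error is on the conservative side: no bias, no excess of false positives, and power of at least 0.90 with 54 analysed per arm if f = 0.18 and r = 0.35 are right. These sizes rest on the assumed R² and on allocation that achieves close balance within strata. The case for a change is that it is nearly free, not that the present model fails.

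**What to change.** State in the Data analysis section that the randomisation strata, child sex and child age (continuous or as banded for randomisation), enter every effectiveness model, in one of two forms:

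- keep the repeated measures model and add age by time and sex by time terms. Main effects alone would leave the interaction test unchanged; or
- use an ANCOVA of the posttest on baseline, condition, age and sex. Here main effects of age and sex are enough, because adjusting for baseline removes only part of a constant effect.

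Name the same covariates in the cost and QALY regressions, for consistency.

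The cost is one or two sentences and two or three degrees of freedom. No new data are needed. If age and sex do not predict change, there is little or no gain, and the loss is negligible: at R² = 0 and N = 108, spending three degrees of freedom leaves power at 0.902.

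### For the two-wave observed primary outcomes, the condition-by-time test is valid but inefficient at the plan's own r = .35; adjusting for baseline would be more precise at almost no cost

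*Protocol article*

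**What the plan says.** The Data analysis section of the protocol article states, for all key outcomes, "we propose the use of a repeated measure ANOVA", with condition as the between-subjects factor and assessment time as the within-subjects factor. The treatment effect is the interaction: "The regression coefficient for the interaction between condition and assessment time will estimate differential changes in parental sensitivity and sensitive discipline". No baseline covariate is named.

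Three other sections matter here:

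- **Instruments.** Observed sensitivity and discipline are collected at baseline and posttest only. The 6-month follow-up uses questionnaires alone.
- **Recruitment.** The sample size rests on an effect of f = .18 and on "power = .90, and *α* = .05, and correlation between pretest and posttest of *r* = .35, at least 54 participants per group are required". The target is then raised: "To account for attrition, we set a target of 60 per group".
- **Study design.** Allocation follows baseline: "group assignment will be done after the baseline assessment is completed to minimize potential bias".

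**The concern.** In a randomised trial whose baseline score is taken before allocation, there are three simple ways to compare arms on a posttest score: ignore baseline, subtract it (the change score), or adjust for it by regression (ANCOVA). All three are unbiased for the treatment effect. They differ in precision, and the ranking depends on the pre-post correlation.

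Subtracting baseline in full is close to the best adjustment only when the correlation is high. At r = .35 a parent who starts one unit above average is expected to finish only 0.35 units above average, so the change score removes 0.65 units too much. The over-correction adds noise. With equal SDs and r below .5, it adds more noise than the subtraction removes, and ignoring baseline would be the more precise choice.

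At stake is the width of the confidence interval for the primary outcomes of a 120-family trial that already collects the score needed to narrow it.

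**Working it through.** **Inputs.** f = .18, power .90, alpha .05, r = .35 and 54 per group come from Recruitment. Two time points for the observed outcomes come from Instruments. Equal pretest and posttest SDs are an assumption, since the article gives no SDs; it is varied in step 5.

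**1. Reproduce the plan's figure.** For the interaction in a design with 2 groups and m = 2 measurements, lambda = f² × N × m / (1 − r), with 1 and N − 2 degrees of freedom. At N = 108, lambda = 0.0324 × 108 × 2 / 0.65 = 10.77 and power is 0.902. This is the smallest even N that reaches 0.90, so 54 per group is reproduced. A between-groups test gives 111 per group, and three measurements give 44. The sample size was therefore computed for the two-wave interaction.

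**2. The effect this implies.** In this parameterisation the four cell means depart from additivity by ±f SD, so the difference in change is 4f = 4 × 0.18 = 0.72 SD. Check: 0.72 / √(1.30 × 2/54) = 3.281, and 3.281² = 10.77, which equals lambda.

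**3. Variance per participant, in units of the outcome variance, at r = .35 and equal SDs.**

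| Analysis | Formula | Value |
|---|---|---|
| Change score (the planned interaction) | 2(1 − r) | 1.30 |
| Posttest only | 1 | 1.00 |
| ANCOVA | 1 − r² | 0.8775 |

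- Change against ANCOVA: 1.30 / 0.8775 = 2/(1 + r) = 1.481, or 48% more variance. The standard error is √1.481 = 1.217 times as large.
- Change against posttest only: 1.30 / 1.00, or 30% more.
- Decomposition: 0.8775 + 0.65² = 1.30 and 0.8775 + 0.35² = 1.00. The excess is exactly the over- or under-correction for baseline.

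A simulation of 20,000 trials at 54 per group gave ratios of 1.46 and 1.30. The 1.46 is slightly below 1.48 because ANCOVA must estimate its slope.

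**4. What this means for the planned effect of 0.72 SD (noncentral t).**

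| Analysis | Power at 54 per group | n per group for 90% |
|---|---|---|
| Change score | 0.902 | 54 |
| Posttest only | 0.960 | 42 |
| ANCOVA | 0.977 | 37 |

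**5. Sensitivity to the assumptions.** Let q be the pretest SD divided by the posttest SD. At r = .35 the change-score variance is 1 + q² − 0.7q in posttest-variance units.

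| q | Change-score variance | Excess over ANCOVA | Against posttest only |
|---|---|---|---|
| 0.5 | 0.90 | 3% | more precise |
| 0.7 | 1.00 | 14% | equal |
| 0.8 | 1.08 | 23% | less precise |
| 1.0 | 1.30 | 48% | less precise |
| 1.2 | 1.60 | 82% | less precise |

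At equal SDs the excess over ANCOVA, 2/(1 + r) − 1, is 33% at r = .5 and 18% at r = .7. The change score beats posttest only once r exceeds .5.

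**The case against.** The strongest reply is that nothing here is wrong. The interaction test is valid under randomisation, it matches a hypothesis worded as change from before to after the intervention, and the sample size was computed for it. On the plan's own inputs it reaches 90% power at 54 per group, and the target is 60. All of that stands. The point is about efficiency, and chance baseline imbalance enters only as lost precision, not as bias.

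The size also needs conditions. The 48% and the comparison with posttest only rest on equal SDs, and r = .35 is a planning value that need not hold for each of the five observed scales. That also stands, so ranges are given. What survives is the direction against ANCOVA: apart from the small cost of estimating one slope, the change score is not the more precise analysis at any SD ratio or correlation.

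Two stronger readings are tempting.

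- **That the trial is short of power.** A reader might infer this by taking f = .18 as half of a standardised posttest difference (2 × 0.18 = 0.36 SD). The article does not say how f was derived from the cited meta-analysis, and the 54 per group corresponds to 0.72 SD. The shortfall does not follow from the stated inputs.
- **That the 48% applies to every outcome under the same model.** The SDQ, DASS-21 and CRPR-Q have three waves, their interaction has 2 degrees of freedom, and no correlations are given for them. The figure does not carry over.

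One loose end: the Objectives section also mentions six months for sensitivity and discipline. The two-wave reading follows Instruments, and the reproduced sample size agrees with it.

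**Conclusion.** The point holds for the observed primary outcomes as a recommended improvement in precision. The planned test is unbiased and consistent with its sample size, but at r = .35 and equal SDs it carries 48% more variance than baseline-adjusted ANCOVA and 30% more than posttest scores alone. Over SD ratios of 0.7 to 1.2 the excess over ANCOVA runs from about 14% to 82%; the disadvantage against posttest only needs a ratio above 0.7. On the effect the trial was sized for, the gain is from about 90% to 98% power at 54 per group. These results rest on r = .35, on two measurement waves and, for the headline figures, on equal SDs. They do not show an invalid analysis or an underpowered trial.

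**What to change.** For each observed scale, make the primary analysis a regression of the posttest score on condition and the baseline score of the same scale, and report the adjusted mean difference with its 95% CI. Because allocation follows baseline, the adjustment is valid.

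Keep 60 per group. Add a sentence to Recruitment saying that the calculation was made for the interaction test and is conservative for the new analysis at the assumed correlation.

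For the three-wave questionnaires, use the analogous mixed model: posttest and 6-month scores as outcomes, with condition, time, their interaction and the baseline score as covariate. Claim no particular percentage gain there.

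The cost is a change of wording in Data analysis, the note in Recruitment, and an update of the registration if it describes the model. No new data are needed. The change should be dated and made before any outcome comparison between arms; recruitment is expected to run until the end of July 2026.
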